**Fig. 2 Fig2:**
[figure not shown]
Different needling angles

**Fig. 3 Fig3:**
[figure not shown]
Head and body

### Patient recruitment

A total of 112 GAD patients will be recruited through, but not limited to, posters pasted in the hospital lobby and social media (WeChat), which can be seen by potential patients. Meanwhile, we will cooperate with the gynecology and psychology departments of the hospital for potential patients to ensure the target sample size is reached. Eligible patients who meet the inclusion criteria and exclusion criteria will be enrolled in the outpatient department of the First Affiliated Hospital of Guangzhou University of Chinese Medicine.

### Inclusion criteria

Patients who meet all of the following criteria will be allowed to enrollment:
Aged 45 to 55 years old (female only).Meet the diagnostic criteria of DSM-5 [1] for GAD.Excessive anxiety and worry (apprehensive expectation), occurring more days than not for at least 6 months.The individual finds it difficult to control the worry.The anxiety and worry are associated with three (or more) of the following six symptoms (with at least some symptoms having been present for more days than not for the past 6 months):Restlessness or feeling keyed up or on edge.Being easily fatigued.Difficulty concentrating or mind going blank.Irritability.Muscle tension.Sleep disturbance (difficulty falling or staying asleep, or restless, unsatisfying sleep).(4)The anxiety, worry, or physical symptoms cause clinically significant distress or impairment in social, occupational, or other important areas of functioning.(5)The disturbance is not attributable to the physiological effects of a substance (e.g., a drug of abuse, a medication) or another medical condition (e.g., hyperthyroidism).(6)The disturbance is not better explained by another mental disorder (e.g., anxiety or worry about having panic attacks in panic disorder).(7)The score of HAMA is between 14 and 28.(8)No anti-anxiety drugs or other psychotropic drugs in the last 2 weeks.(9)No participation in any other research in the last 1 month.

### Exclusion criteria

Patients who meet any of the following criteria will be excluded:
Diagnosed by other severe illnesses such as heart failure, tumors, renal failure, and so on.Diagnosed by psychotic illness such as schizophrenia, agoraphobia, and so on clearly.Addicted to alcohol or drugs in the past 3 months.Afraid of acupuncture.Pregnancy or breastfeeding.

### Drop out criteria

Patients who meet any of the following criteria will be excluded from the study:
Cannot complete all treatment sessions.Outbreaks of serious illness threatening life include disability, cancer, organ failure, and so on.Unwilling to comply with acupuncture treatment.Anti-anxiety drugs or other psychotropic drugs were administered when enrolled in the study.Pregnancy when enrolled in the study.Patient quits the study treatment by herself.

### Inventions

All eligible patients will receive 12 sessions of MA or PA (4 weeks, three times a week). Each session will take 30 min. The acupuncture therapists have acupuncture education from Guangzhou University of Chinese Medicine (range 1–3 years of full-time academic studies) or have clinical experience in the First Affiliated Hospital of Guangzhou University of Chinese Medicine (range 2–5 years). In addition, all intervenors are trained to completely understand the standard of operation. The acupoints of the MA and PA groups are the same, including Sishenzhen (one of the main acupoints in Jin’s 3 Needle [22]), Shenting (DU24), Yintang (DU29), Shenmen (HT7), and Sanyinjiao (SP6). The acupoint locations are according to the “2006 People’s Republic of China National Standard” (GB/T1234-2006) with the exhibition in Fig. 4. The acupuncture operation will be performed according to the textbook of the 10th Five-Year Plan of the Ministry of Health. Enrolled patients will be treated one-on-one by a trained acupuncturist from beginning to the end. In addition, an independent assistant will follow the intervention procedures to ensure the consistency of treatment.

**Fig. 4 Fig4:**
[figure not shown]
Acupoint locations

### MA group

Patients in the MA group will be pricked by disposable, stainless steel needles (φ0.30 × 40 mm, produced by Huanqiu Co. Ltd., China) through our device. The needles will be inserted into the skin to ensure that patients have a Deqi sensation [23] which is considered the essential reason for the efficacy of acupuncture [24]. Depth of puncture is approximately 25–30 mm. The needles will be manipulated three times (at the start, middle, and end of every session) by twirling and lifting until the Deqi sensation occurs.

### Placebo acupuncture (PA) group

Patients in the PA group will receive placebo acupuncture in which the needles will not be inserted into the skin and will not induce the Deqi sensation. The blunt-tipped placebo needle (φ0.30 × 40 mm, produced by Huanqiu Co. Ltd., China) can provide participant-blinding effects with a similar appearance to conventional needles but no skin penetration.

### Outcome measure

The schedule of the whole procedure is shown in Fig. 5. An independent assessor who does not know the group assignment will collect outcome data for analysis.

**Fig. 5 Fig5:**
[figure not shown]
The schedule of the whole procedure

### Primary outcome

#### HAMA score

The primary outcome of this study is the HAMA [25] score, which measures the severity of anxiety. The HAMA is a 14-item scale rated on a 4-point scale with a total score ranging from 0 to 56. A higher score means a higher range of anxiety. According to studies, a score higher than 28 indicates severe anxiety, a score between 28 and 21 indicates moderate anxiety, a score between 20 and 14 indicates mild anxiety, and a score lower than 14 indicates no anxiety. HAMA will be assessed on the first day, the 14th day, and the 28th day of the trial.

### Secondary outcome

#### GAD-7 score

The secondary outcome of this study is the GAD-7 [26] score, which measures the severity of GAD particularly. The GAD-7 is a 7-item scale rated on a 3-point scale with a total score ranging from 0 to 21. In addition, the GAD-7 score indicates the level of general anxiety. The higher the GAD-7 score is, the more anxious the patient is. If the patient is enrolled, GAD-7 will be assessed on the first day, the 14th day, and the 28th day of the trial.

#### PSQI score

The secondary outcome of this study is the PSQI [27] score, which measures the quality of sleep in the last month. The PSQI is a 19-item questionnaire, divided into 7 parts: sleep quality, sleep latency, sleep duration, habitual sleep efficiency, sleep disturbances, use of sleeping medication, and daytime dysfunction. The PSQI score is inversely proportional to the quality of sleep. PSQI will be assessed on the first day, the 14th day, and the 28th day of the trial.

#### CORT and ACTH

It has been suggested that anxious subjects demonstrate greater CORT and ACTH concentrations [28]. In this study, we will draw serum samples and investigate CORT and ACTH before and after acupuncture. An enzyme-linked immunosorbent assay (ELISA) will be used to measure CORT and ACTH. These related tests will be carried out by the clinical laboratory of the First Affiliated Hospital of Guangzhou University of Chinese Medicine.

### Safety outcome

Researchers will record body temperature, respiratory rate, pulse rate, and blood pressure on the first day, the 14th day, and the 28th day of the treatment. Adverse events (AEs) caused by acupuncture should be truthfully recorded in case report forms (CRFs). In addition, intervenors should treat patients with AEs as soon as possible to comfort patients and eliminate AEs. In the meanwhile, we will inform AEs to the Ethics Committee of the First Affiliated Hospital of Guangzhou University of Chinese Medicine. After treatment of AEs, researchers will ask patients whether they would like to continue the trial or not and respect their will.

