### Sample size

According to preliminary trials [20, 21], we chose the HAMA score as the outcome to calculate the sample size. After treatment, the HAMA score of MA was 14.0±3.2, and the HAMA score of PA was 19.4±5.3. PASS version 15.0 (NCSS, LLC. Kaysville, UT, USA) was used to estimate the sample size with a power level of 90% and a two-sided significance level of 5%. After calculation, we set the sample size of 44 patients in each group to observe the significant difference between the two groups. With a 20% withdrawal rate, we plan to enroll a total of 112 patients with 56 patients in each group.

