### Randomization and allocation concealment

An independent researcher sets a random number as a seed and used IBM SPSS Statistics version 26 (IBM SPSS Inc., Chicago, USA) to generate a random allocation sequence. According to the size of the random number sequence, patients who received the first 56 random numbers will be allocated into the MA group, and patients who received the last 56 random numbers will be allocated into the PA group in a 1:1 ratio. The researcher will put the cards with written random numbers and group assignments into sealed envelopes. The intervenors will allocate enrolled patients into the MA group or PA group on the basis of the card in the envelope.

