This study has room for improvement. First, due to the nature of acupuncture, we spare no effort to maintain blinding, but we still cannot find a perfect way to achieve double blinding. We can make the pedestal of acupuncture needles that look the same and simulate the feeling of being needled by touching with semi blunt needles. Therefore, patients are unaware of whether they receive MA or PA. However, experienced acupuncturists can feel the difference in whether needles prick the skin and achieve Deqi or not. Second, this study is a single-center trial, and we hope that this study will provide more clinical evidence and design a multi-center trial to confirm the efficacy of acupuncture in treating GAD.

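### The Safety outcome section makes attribution to acupuncture a condition for recording an adverse event, so unattributed events are lost in both arms and the safety comparison may be distorted

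*Protocol article*

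**What the plan says.** Under Safety outcome, the protocol article sets two recording tasks. The first covers vital signs: "Researchers will record body temperature, respiratory rate, pulse rate, and blood pressure on the first day, the 14th day, and the 28th day". These are taken whatever the cause of any change. The second covers adverse events: "Adverse events (AEs) caused by acupuncture should be truthfully recorded in case report forms (CRFs". The same section adds that "intervenors should treat patients with AEs as soon as possible to comfort patients and eliminate AEs", that AEs are reported to the Ethics Committee, and that the patient is then asked whether she wishes to go on. It does not say who decides that an event was caused by acupuncture, or who makes the entry.

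Three other statements bear on this rule:

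- Randomization and allocation concealment: "The intervenors will allocate enrolled patients into the MA group or PA group on the basis of the card in the envelope".
- Discussion: "experienced acupuncturists can feel the difference in whether needles prick the skin and achieve Deqi or not".
- Placebo acupuncture (PA) group: "Patients in the PA group will receive placebo acupuncture in which the needles will not be inserted into the skin".

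**The concern.** A safety record is normally built in two steps: write down every untoward event, then judge whether treatment caused it. Here the judgement comes first and decides whether there is a record at all. This has two consequences.

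- **Loss in both arms.** An event that nobody links to needling when it occurs leaves no AE entry. If a pattern emerges later, it cannot be reassessed, because the data were never collected.
- **Possible difference between arms.** If the person attributing events knows the arm, causation is easier to affirm where a needle entered the skin than where it did not. The same dizziness or headache could be entered under MA and left out under PA. MA would then look less safe relative to PA than it is.

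At stake is the descriptive comparison of AEs by arm, and what the Ethics Committee gets to see. The efficacy analysis is not touched.

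**Working it through.** The article states no AE rate and no safety figure, so there is nothing to reproduce. The check is a reading of the text, followed by simple algebra.

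**Step 1. Does anything widen AE capture?** No. The later sentences under Safety outcome speak of AEs without qualification, but they concern treating and reporting them, and they set no second recording rule. Data monitoring and analysis and Quality control deal with storage, double entry and form checks. Vital signs are the only item in the safety section recorded regardless of cause.

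**Step 2. Could attribution differ by arm?** Yes.

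- The intervenors allocate from the card, so they know the arm.
- The Discussion concedes that an experienced acupuncturist can feel whether the needle penetrates.
- The intervenors are also the people told to treat AEs, so they are likely to be among the first to learn of them.
- The PA needle has a "similar appearance to conventional needles but no skin penetration", so a causal link is less readily affirmed in that arm.
- Outcome measure provides a blinded assessor for outcome data, but gives that person no stated part in judging AE causality.

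**Step 3. How would this act on the counts?** Let *n* be the patients per arm, *r* the true proportion with an event (the same in both arms), and *a* the probability that an event is judged caused by acupuncture. Then

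- recorded per arm = *n* × *r* × *a*
- unrecorded per arm = *n* × *r* × (1 − *a*)
- spurious difference in recorded risk = *r* × (*a*_MA − *a*_PA)

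The article gives *n* = 56 (Sample size: "we plan to enroll a total of 112 patients with 56 patients in each group"). It gives neither *r* nor *a*. Every value of *r* and *a* below is an assumption, chosen to show the mechanism and not to estimate it.

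| *r* | *a*, MA / PA | Recorded MA | Recorded PA | Difference |
|---|---|---|---|---|
| 10% | 80% / 80% | 4.5 | 4.5 | 0 |
| 10% | 80% / 50% | 4.5 | 2.8 | 3 points |
| 10% | 80% / 20% | 4.5 | 1.1 | 6 points |
| 20% | 80% / 80% | 9.0 | 9.0 | 0 |
| 20% | 80% / 50% | 9.0 | 5.6 | 6 points |
| 20% | 80% / 20% | 9.0 | 2.2 | 12 points |

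For example, 56 × 0.20 × 0.80 = 9.0, 56 × 0.20 × 0.50 = 5.6, and 0.20 × (0.80 − 0.50) = 0.06.

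Two results hold whatever the values. If *a* is below 1, events are lost: with *r* = 20% and *a* = 80% in both arms, 56 × 0.20 × 0.20 = 2.2 per arm go unrecorded even though the arms show no difference. A spurious difference arises only if *a* differs between arms, and its size is set wholly by quantities that the article does not give.

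**The case against.** The strongest reply is that this is condensed prose. The sentence asks for truthful recording of acupuncture-related events and does not contain the word only. Definitions, solicitation and causality fields usually sit in the full protocol and the form, which are not shown. That would answer a complaint about silence. But the article is not silent: it states a rule with a causal qualifier, and nothing else in it broadens that rule. The restrictive reading is an inference, but it is the plain one.

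Other parts of the reply stand, and they limit what can be claimed:

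- **Who judges is not stated.** Intervenors treat AEs, but no section says that they attribute or enter them. Data monitoring and analysis has assessors recording data, and Outcome measure keeps the outcome assessor blind. A reader might infer that AE counts will simply mirror the beliefs of unblinded staff. The text makes that possible and does not establish it.
- **PA events need not vanish.** Blinding describes a blunt needle meant to feel like a prick, and an adhesive base. Local pain or a skin reaction could well be attributed to the procedure.
- **Worsening anxiety or sleep is not unseen.** A reader might list these among the lost harms. HAMA, GAD-7 and PSQI measure them in both arms on days 1, 14 and 28, and at the one- and three-month follow-up.
- **Grave illness is not wholly unseen.** Drop out criteria name life-threatening illness, so such events have to be noticed whatever their cause, though not as AEs.
- **No between-arm AE test is described.** False-positive rates for such a test would therefore be beside the point.

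**Conclusion.** The point holds as a defect in a stated rule. As written, a causality judgement precedes recording, and events not attributed to needling are not captured as AEs in either arm. This rests only on the plain reading of one sentence and the absence of any wider rule.

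The second part is weaker. Attribution may differ by arm, probably leading to undercounting in PA, and this could distort the descriptive safety comparison. It assumes that the judgement is made or influenced by someone who knows the arm, which the article neither states nor prevents.

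No size can be given. A reader might infer a spurious MA excess of 10 to 20 percentage points by assuming that 10% to 20% of patients have an event and that all are recorded in MA and none in PA. The article supports neither the event rate nor such an extreme split, so that figure should not be used. The likely direction would count against MA, so the rule does not flatter the treatment under test. The change is worth making because it is cheap and because events never written down cannot be reliably reconstructed later.

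**What to change.** Replace the recording sentence under Safety outcome with: *All adverse events, whether or not thought related to acupuncture, will be recorded in both arms with the same open question at day 14, day 28 and each follow-up contact; seriousness and relatedness will be recorded afterwards as separate fields.* State who judges relatedness, preferably someone blind to the arm.

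Two safeguards are needed:

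- **Protect the HAMA rating.** Ask the question only after HAMA has been scored at that contact, since mention of bruising or needle marks could reveal the arm. A day 14 answer could still colour the day 28 rating, so someone other than the HAMA rater should ask if staffing allows.
- **Split the reporting period.** Report all-cause and related AEs by arm, with events up to day 28 separate from later ones. Ancillary and post-trial care gives PA patients a course of 12 MA sessions after treatment, so later events in that arm may come from real needling.

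The cost is one sentence, two form fields, a short question at contacts already planned, and slightly more entries. The split by period adds one line to the safety tables.

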### Ancillary and post-trial care

After the whole treatment, patients who received PA treatment will receive 12 sessions of MA treatment to compensate. If patients who receive MA treatment want to continue treatment, they can appoint and be treated in the outpatient department.

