**Methods:**

This study is a single-center, randomized, single-blind clinical trial that will be conducted in the First Affiliated Hospital of Guangzhou University of Chinese Medicine. A total of 112 eligible GAD patients will be randomly assigned (1:1) to receive MA (*n*=56) or PA (*n*=56) three times per week for 4 weeks. The primary outcome measure will be the HAMA score. The secondary outcome measures will be the GAD-7 and PSQI scores and the levels of CORT and ACTH. The evaluation will be executed at baseline, 2 weeks, the end of the treatment, and a follow-up 3-month period. All main analyses will be carried out based on the intention-to-treat (ITT) principle.

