## Methods

### Study design

This is a randomized controlled and patient-and-assessor-blind trial. A total of 112 participants will be enrolled from the outpatient Acupuncture and Moxibustion Department of the First Affiliated Hospital of Guangzhou University of Chinese Medicine. The flow chart is shown in Fig. 1. The protocol is composed based on the SPIRIT checklist [18] and the Declaration of Helsinki [19]. The trial was approved by the Ethics Committee of the First Affiliated Hospital of Guangzhou University of Chinese Medicine (K[2021]014) and has been registered at the Chinese Clinical Registry (ChiCTR2100046604).

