### Follow-up

After the completion of 12 sessions of acupuncture, we will follow patients via telephone or WeChat to score the HAMA, GAD-7, and PSQI scores in the first month and the third month to determine whether the efficacy can be maintained.

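### As worded, the 12 compensatory MA sessions for PA patients can fall before the month-1 and month-3 scores, so follow-up may not compare MA with PA or cleanly show maintained efficacy

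*Protocol article*

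**What the plan says.** Five places in the protocol article bear on this.

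- **Ancillary and post-trial care**, PA arm: "After the whole treatment, patients who received PA treatment will receive 12 sessions of MA treatment to compensate". No start date or session rate is given.
- **Ancillary and post-trial care**, MA arm: "If patients who receive MA treatment want to continue treatment, they can appoint and be treated in the outpatient department". The amount is left open.
- **Inventions** (the interventions section) defines the treatment: "All eligible patients will receive 12 sessions of MA or PA (4 weeks, three times a week".
- **Follow-up** starts when that treatment is complete: "After the completion of 12 sessions of acupuncture, we will follow patients via telephone or WeChat to score the HAMA, GAD-7, and PSQI scores". The scores are taken "in the first month and the third month to determine whether the efficacy can be maintained".
- **Abstract, Methods** treats the end of treatment and the follow-up as separate: "The evaluation will be executed at baseline, 2 weeks, the end of the treatment, and a follow-up 3-month period".

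The primary outcome section sets its own visits within the treatment period: "HAMA will be assessed on the first day, the 14th day, and the 28th day of the trial". The study design section says: "This is a randomized controlled and patient-and-assessor-blind trial".

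**The concern.** The compensatory course and the follow-up clock are tied to the same event, the end of the 12 trial sessions. If both start there, control patients receive the test treatment during the period meant to show whether its benefit lasts.

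Three things are then at stake at months 1 and 3:

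- **The contrast.** PA patients with real MA behind them are no longer a placebo group. The better MA works, the more the difference between arms is erased, and a small difference could be misread as loss of efficacy.
- **Maintenance within the MA arm.** Stable MA scores could reflect further MA by appointment and not a lasting effect of the 12 trial sessions.
- **Blinding.** A course given only to PA patients, as compensation, probably tells them what they had received. All three scales depend on what the patient reports.

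The Data monitoring and analysis section applies between-group and repeated-measures tests to HAMA, GAD-7 and PSQI without saying which visits enter, and says nothing about patients who have crossed over.

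**Working it through.** No stated figure in the plan decides this point. The check sets the timing statements side by side and then shows what they would imply for the size of the difference.

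**1. Order of events.** Inventions fixes the treatment as 12 sessions over 4 weeks. Ancillary and post-trial care places the compensatory MA after the whole treatment. Follow-up begins on completion of 12 sessions. The Abstract lists end of treatment and follow-up separately, so *treatment* most naturally means the 4 weeks and does not include the follow-up. Nothing in the text shown delays the compensatory sessions until after month 3.

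**2. Exposure of PA patients at each follow-up visit.** The start delay *s* (weeks after the end of treatment) and the rate *r* (sessions per week) are not stated, so both are assumptions. Taking a month as 4 weeks, the number of MA sessions received by week *t* of follow-up is min(12, r × (t − s)), and zero if s ≥ t. Month 1 is t = 4 and month 3 is t = 3 × 4 = 12.

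| Assumed s | Assumed r | MA sessions by month 1 | MA sessions by month 3 |
|---|---|---|---|
| 0 | 3 | 3 × 4 = 12 | 12 |
| 2 | 3 | 3 × 2 = 6 | 12 |
| 4 | 3 | 0 | 12 |
| 8 | 3 | 0 | 3 × 4 = 12 |
| 10 | 3 | 0 | 3 × 2 = 6 |
| 0 | 1 | 1 × 4 = 4 | 12 |
| 12 or more | any | 0 | 0 |

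Only the last row leaves both visits free of MA in the PA arm. With an immediate start at the trial's own rate, 12 / 3 = 4 weeks, so the full course is done at about month 1. Up to 56 of 112 patients, the whole control arm, are eligible for it.

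**3. Possible size.** The Sample size section gives HAMA 14.0 (SD 3.2) for MA and 19.4 (SD 5.3) for PA.

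- Planned difference: 19.4 − 14.0 = 5.4 points.
- Common SD: √((3.2² + 5.3²)/2) = 4.38.
- Let *f* be the share of the difference lost at follow-up once PA patients receive MA. The documents give no value for *f*. The remaining difference is 5.4 × (1 − f).
- Power is for 44 per arm, two-sided 5%, with the SD assumed unchanged at follow-up.

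| f (assumed) | Remaining difference | Power |
|---|---|---|
| 0 | 5.40 | above 99.9% |
| 0.25 | 4.05 | 99% |
| 0.5 | 2.70 | 82% |
| 0.75 | 1.35 | 30% |
| 0.9 | 0.54 | 8% |
| 1 | 0 | 5% (type I error only) |

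The 44 per arm is taken as stated. The plan's inputs do not reproduce it: they give 14 per arm by the normal formula and 15 by the t-test. That is a separate matter, and this point does not depend on it.

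**4. What is not touched.** HAMA, GAD-7 and PSQI are scheduled on days 1, 14 and 28. Compensatory MA follows the 4-week treatment, so these scores precede it.

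**The case against.** The strongest reply is that the order is not actually stated. The section heading speaks of post-trial care, and the Abstract counts the 3-month follow-up among the trial's evaluations, so the compensatory sessions may be meant to follow month 3. The schedule figure and flow chart are not shown, and the article condenses a fuller protocol. This stands as far as intent goes. It does not remove the problem, because the sentence under the heading points to the end of treatment and the text never says otherwise.

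The session rate is also borrowed: three a week describes the trial sessions only. That stands too. It matters less for month 3, because even one session a week from the end of treatment completes the course by then.

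A reader might go further and infer any of the following:

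- **Both follow-up visits are certainly contaminated and no PA arm is left.** This needs a prompt start, which is not stated.
- **Every patient is told her arm before follow-up scoring.** No passage describes disclosure. Compensation given to one arm makes it likely that PA patients learn their allocation, but that remains an inference. Unblinding of the assessor is possible through telephone or WeChat contact but is not shown.
- **The difference falls to zero.** That requires PA patients to reach an average of 14.0 while MA patients stay there, and the documents support neither.
- **The primary result is compromised.** The HAMA schedule in the primary outcome section ends on day 28, before any compensatory MA.

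Finally, the Follow-up section states a maintenance aim and names no between-arm test at months 1 or 3. A comparison of the randomised arms at those visits also keeps a meaning as immediate versus delayed MA. Both points are fair, and they are why a ban on any between-arm test would go too far. A within-arm look at maintenance still needs the optional further MA to be recorded.

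**Conclusion.** The concern holds for the follow-up objective only. As worded, the compensatory MA and the follow-up start from the same point, and PA patients may have had anything from none to all 12 real MA sessions before a follow-up score. Scores taken after that exposure do not compare MA with PA. Together with the open-ended MA available to the other arm, they cannot cleanly show that efficacy is maintained.

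The numerical effect cannot be fixed from the documents. It runs from no loss, if the sessions follow month 3, to loss of the whole 5.4-point planned difference, if PA patients fully catch up; half lost would leave 2.7 points. The conclusion rests on reading *after the whole treatment* as after the 4-week course, which is the natural reading but not the only possible one. The day-14 and day-28 comparisons stand. This is more than missing detail, because the stated order, if followed, would make a follow-up conclusion about MA versus PA wrong.

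**What to change.** 1. Reconcile the sections Ancillary and post-trial care and Follow-up, so that the order of compensatory treatment and the month-1 and month-3 assessments is explicit. Which order applies is for the investigators to decide.
2. Record the date and number of any post-treatment acupuncture sessions in both arms.
3. State that the randomised MA-versus-PA efficacy claim rests on day 28.
4. Do not present follow-up values obtained after a PA patient has started MA as an MA-versus-PA or maintenance comparison. Report them descriptively, or label them explicitly as immediate versus delayed MA.

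The cost is wording in two sections, a statement in the analysis section and one line on the case report form. No extra patients or visits are needed. The downside is a narrower follow-up claim if the current timing stands.
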